### Study Procedure

Participants randomly assigned to condition A will receive access to the ThinkNinja for Epilepsy app first. Participants will receive guidance on the expected frequency and duration of app use and will be encouraged to use the app two to three times per week for the duration of the 8-week study period. After the active 8-week period of the study is completed, participants may use the app on their own accord, as much as they like, for the remaining 8-week duration of the study.

Step-ups will only be available for the 8-week active participation period of the study. Participants will be reminded via push notifications to use the app if they have not used it in the previous 3 to 7 days. Although participants will be able to disable app notifications as is standard through their device’s operating systems settings menu, we will request that they remain enabled for the duration of the study in order to facilitate communication with the research team. Participants assigned to condition B will receive the same full access to the ThinkNinja for Epilepsy app as the participants in condition A after 8 weeks. The study procedures and timing are summarized in Figures 1 and 2.

We considered performing weekly tracking of anxiety and mood for the control arm participants but, on balance, decided that for this exploratory study, the potential adverse effects on engagement due to perceived burden outweighed the advantages of collection of weekly data. The weekly measures will be collected as part of the CBT-based intervention, as is common in the delivery of CBT; this will allow us to monitor clinical change and potential risk as part of the intervention. Participants will be able to report any app technical issues via a Healios study email address and telephone number. The research team will make every effort to locate participants lost to follow-up using text and email.

**Figure 2 figure2:**
[figure not shown]
Participant flow. Arm A participants will receive access to ThinkNinja for Epilepsy app first. Arm B participants will be the waiting-list control group.

### Sample Size

A formal sample size calculation was based on assumptions of QOLIE-10-P means and SDs from earlier studies [37,38]. It was performed using a 2-tailed *t* test of equal means at a significance level of .05 and a power of 80% for an estimated medium effect size (Cohen *d*=0.5). All calculations were done using the software nQuery (version 7.0; Statsols) [39]. We intend to recruit 184 people—92 participants in each arm—so that we can accommodate a dropout rate of 30%.

The chi-square method was used to determine the power for structural equation modeling (SEM) [40] using the associated online power calculator [41]. It was determined that with a sample size of 184 (see above) and a *P* value of .05, the proposed 11-parameter SEM analysis would be powered at 0.705 (70.5%).

### Data Analysis

The analysis will be performed in two phases. The first phase of analysis will occur after completion of the 8-week (T2) outcome measures, when all participants in arm A have completed the 8-week program and can be compared to the waiting-list control participants (arm B). The second phase of analysis with the pooled data will occur after the completion of the 8-week follow-up period (T3) outcome measures for all participants.

The following patient cohorts will be used in the analysis:

The per-protocol study cohort will include all allocated participants with at least 80% completed questionnaire data, including a completed QOLIE-10-P score, at baseline (T0 ThinkNinja for Epilepsy group and T–1 wait-list group) and at 8 weeks (T2 ThinkNinja for Epilepsy group and T0 wait-list group).The intention-to-treat study cohort will include all allocated participants.

Available information on screened participants who were not randomized will be summarized.

Descriptive statistics will be produced for the distribution of all variables, including baseline demographic variables, app use, and engagement variables, as well as for each outcome variable at each time point. The change in each outcome from baseline will be reported in terms of mean and SD. An analysis of reliable and clinical change will be produced for the GAD-7 and PHQ-9 scores in order to determine the percentage of those who had clinical and reliable change (ie, clinical recovery) after taking part in the intervention.

The primary outcome analysis (ie, quality of life) will be performed for the overall cohort, both unadjusted and adjusted for baseline characteristics, app use, and app content variables. We will be comparing changes in quality of life (ie, QOLIE-10-P scores) from baseline to completion of the 8-week program.

The secondary outcome analysis will constitute analyzing the change in GAD-7 (ie, anxiety) and PHQ-9 (ie, depression) scores. In addition, we will be reporting on the results of the MAQ and PGIC, using descriptive statistics.

In addition to this, a sensitivity analysis that uses both the primary and secondary outcomes will be performed. To explore both between-subjects (ie, arm A vs arm B) and within-subject (ie, T0 vs T1 vs T2 vs T3) differences, a series of repeated-measures (2 × 4) analyses of variance (ANOVAs) will be performed in the first instance with both the primary outcome measure (ie, QOLIE-10-P score) and the secondary outcome measures (ie, GAD-7, PHQ-9, PGIC, and MAQ scores) as dependent variables. All of these ANOVA tests will be powered at 0.80 (*P*=.05). The output from this series of ANOVAs will permit the necessary sensitivity analyses to be completed.

Further exploratory subgroup analyses will be performed for the following:

Change in primary and secondary outcomes for subgroups defined by baseline characteristics and demographics, such as age and gender.Change in primary and secondary outcomes stratified by app use, videoconference use, and text support use.Engagement variables: low versus high frequency and duration of app use.

Responder and nonresponder groups will be identified on the basis of changes in primary and secondary outcomes, and these groups will be characterized in terms of baseline characteristics, demographics, and app use variables. Descriptive statistics will be produced, and a regression model will be performed to identify variables associated with responder status. An SEM model will then be developed where baseline characteristics will be independent variables, app use and content variables will be mediating latent variables, and quality of life will be the dependent variable. Regression coefficients will be reported with 95% CIs. These analyses will be performed as an intention-to-treat analysis, using all randomized participants with imputation of missing end-of-study (T2) observations, with the exception of the sensitivity analyses, which will be per-protocol analyses.

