### Aims of This Study

In this exploratory randomized controlled trial (RCT), we will evaluate whether an 8-week CBT-based intervention, delivered through ThinkNinja for Epilepsy (Healios Ltd), is a clinically effective tool for improving the quality of life, mental health, and emotional well-being in a large sample of people with epilepsy.

We hypothesize the following:

There will be an improvement in participants’ self-reported quality of life scores, as measured by the 10-item patient-weighted Quality of Life in Epilepsy questionnaire (QOLIE-10-P) [28], as a result of the ThinkNinja for Epilepsy intervention.There will be an improvement in participants’ self-reported anxiety, depression, impression of change, and medication adherence, as measured by the 7-item Generalized Anxiety Disorder assessment (GAD-7) [29], the 9-item Patient Health Questionnaire (PHQ-9) [30], the Patient Global Impression of Change questionnaire (PGIC) [31], and the Medication Adherence Questionnaire (MAQ) [32], respectively, as a result of the ThinkNinja for Epilepsy intervention.There will be a positive association between the level of engagement with the app and the primary and secondary outcomes.

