### Study Design

Participants will be randomly assigned to a waiting-list control group or will receive full access to the ThinkNinja for Epilepsy smartphone app. A mixed study design will allow for an initial between-subjects analysis between the two condition arms—those who receive the app straight away versus those who wait for access—as well as a within-subject analysis of those who complete the intervention; this includes those who receive the intervention straight away as well as those who receive it after the waiting period. The study adheres to relevant ethical guidelines from the British Psychological Society [33]. In addition, the completeness, content, and quality of the study protocol is reported in line with the Standard Protocol Items: Recommendations for Interventional Trials guidelines [34].

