### Outcomes and Variables

Figure 1 shows details of the measures and the time points at which they will be collected. The primary outcome is the QOLIE-10-P score.

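### The primary-analysis wording reads as a pooled pre-post change, does not match the two-group test that sized the trial, and leaves unstated which contrast decides hypothesis 1

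*Protocol article*

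**What the plan says.** - **Outcome and hypothesis.** Outcomes and Variables: "The primary outcome is the QOLIE-10-P score". Aims of This Study: "There will be an improvement in participants’ self-reported quality of life scores, as measured by the 10-item patient-weighted Quality of Life in Epilepsy questionnaire", attributed to the intervention. No comparator is named.
- **Design.** Study Design: "A mixed study design will allow for an initial between-subjects analysis between the two condition arms", followed by a within-subject analysis of everyone who completes the app, whether at once or after waiting.
- **Sample size.** "It was performed using a 2-tailed *t* test of equal means", "at a significance level of .05 and a power of 80"%, with Cohen d 0.5, 92 per arm and 30% dropout.
- **Phases.** Data Analysis puts the comparison of arm A with the waiting list first, at 8 weeks. Then: "The second phase of analysis with the pooled data will occur after the completion of the 8-week follow-up period (T3) outcome measures".
- **Primary analysis.** Data Analysis: "The primary outcome analysis (ie, quality of life) will be performed for the overall cohort, both unadjusted and adjusted". The adjustment set is baseline characteristics, app use and app content. The quantity is change in QOLIE-10-P from baseline to the end of the program. No arm term and no phase are given.
- **Windows and imputation.** The randomised 8-week window (arm A T0 to T2, arm B T–1 to T0) appears in the per-protocol cohort definition. The intention-to-treat statement at the end of Data Analysis imputes missing T2 values.
- **Arm A versus arm B as a named test.** This appears only for the 2 × 4 repeated-measures ANOVAs, which are introduced as sensitivity analysis.

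**The concern.** The sentence that should define the primary analysis describes something other than the test on which the trial was sized. Four features point towards a pooled pre-post change:

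1. It refers to the cohort as a whole, which is neither of the two cohorts the section defines, and has no arm term.
2. Arm B completes the program only after its waiting period, so change to program completion in arm B lies outside the randomised comparison.
3. App use and app content do not exist for arm B while it waits, so they fit pooled data better than a between-arm model.
4. The imputation targets T2. Outcomes and Variables defines T2 as 8 weeks after starting the app, so in arm B it falls after app access. Arm B's value at the end of the randomised period is its T0.

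At stake is what a positive result would mean. The between-arm contrast is protected by randomisation and a concurrent control. The pooled change is not: natural improvement, or regression to the mean after entry on GAD-7 of 5 or more, would be counted as benefit of the app.

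**Working it through.** **1. The plan's own figure.** Inputs from Sample Size: d = 0.5, two-sided .05, power 80%, dropout 30%.
- Two-sample t test: 63.77, so 64 per arm (power 80.1%).
- Dropout: 64 / 0.70 = 91.4, so 92 per arm and 184 in total. This matches the stated figure.

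The trial is therefore sized for a comparison of two independent groups.

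**2. Set-up for the two contrasts.** Assumptions, not in the documents: SD 1 at each visit, equal correlation ρ of 0.5 or 0.7 between visits, 64 completers per arm, no app effect, and a paired t test for the pooled change (the article names no test for phase 2).
- Between-arm: change in A (T0 to T2) minus change in B (T–1 to T0).
- Pooled: mean of the 128 on-app changes (A T0 to T2; B T0 to T2).
- Variance of one change: v = 2(1 − ρ), so SD 1.000 at ρ = 0.5 and 0.775 at ρ = 0.7.

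**3. Pooled test with drift and no app effect.** Drift is 0.2 SD in each 8-week period. Rejection is approximately Φ(0.2 / SE − 1.979), with SE = SD / √128.
- ρ = 0.5: SE 0.0884; 0.2 / 0.0884 = 2.26; Φ(0.28) = 0.61.
- ρ = 0.7: SE 0.0685; 0.2 / 0.0685 = 2.92; Φ(0.94) = 0.83.

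Simulation (8,000 trials per setting) gave 61.6% and 82.5%. The between-arm test stayed at 5.1% and 4.9%, because equal drift cancels. The pooled test was significant and the between-arm test was not in 59% and 80% of trials.

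**4. Range over the assumptions (simulated, pooled test).**

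| Drift | 64 per arm, ρ 0.5 to 0.7 | 92 per arm, ρ 0.5 to 0.7 |
|---|---|---|
| 0.1 SD in each period | 20% to 30% | 27% to 41% |
| 0.2 SD, in the first 8 weeks only | 20% to 30% | 28% to 41% |
| 0.2 SD in each period | 62% to 83% | 77% to 94% |
| 0.3 SD in each period | 92% to 99% | 98% to 100% |

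**5. If either contrast could count, with no drift.** Arm B's two successive changes share its T0 value, with covariance −(1 − ρ) = −v/2.
- Covariance of the two estimates: v/(2n) + v/(4n) = 3v/(4n).
- Variances: 2v/n (between-arm) and v/(2n) (pooled).
- Correlation: (3/4) / √(2 × 1/2) = 0.75.

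Two standard normal statistics with correlation 0.75, each tested at two-sided .05, give at least one rejection in 8.1% of trials (simulated 8.0% to 8.4%). Under independence the figure would be 1 − 0.95² = 9.75%.

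**The case against.** The article points to the between-arm contrast in several places. The sample size is a two-group t test with 92 per arm, the between-subjects analysis comes first, and the per-protocol windows would not fit a pooled pre-post test. The reference to the cohort as a whole may only mean that the analysis is not by subgroup, since exploratory subgroup analyses follow. The trial calls itself exploratory, and a hierarchy or alpha split may sit in an analysis plan that is not shown.

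Most of this stands. The between-arm contrast was probably intended, and a missing alpha split is not in itself a finding. A reader might go further and infer that hypothesis 1 has two chances at full alpha, or that the authors chose the pooled change as primary. The documents support neither. No passage says that a pooled result, or either result, would be enough, and the claim that improvement results from the app suits a randomised comparison. The 8% figure is therefore conditional, and the drift figures describe a risk only if the pooled change is used.

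What the objection does not remove is the mismatch. The article does describe its primary analysis, and app-use adjustment, change to program completion and T2 imputation do not fit the randomised contrast. That is a point stated badly, not one left out for brevity. The exploratory label does not settle it either, because the article states a hypothesis, sizes a two-sided test for it and aims to determine clinical efficacy.

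**Conclusion.** The point holds in limited form. The primary-analysis wording does not match the test that sized the trial. The randomised contrast is implied as primary but never stated to be the one that decides hypothesis 1. If the pooled change were used, it could be significant with no app effect in about 61% to 83% of trials, given an assumed drift of 0.2 SD in each period, ρ of 0.5 to 0.7 and 64 per arm. The figure is about 20% to 30% if drift is confined to the first 8 weeks. If either contrast could count and there were no drift, the error rate would be about 8% rather than 5%. Drift, correlation and the form of the pooled test are assumptions. The mismatch in wording does not depend on them.

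**What to change.** Replace the primary-analysis sentence in Data Analysis so that it states:

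- Hypothesis 1 is decided solely by the phase-1 between-arm comparison of change in QOLIE-10-P over the randomised 8 weeks (arm A T0 to T2, arm B T–1 to T0), in all randomised participants, at two-sided .05.
- One pre-named model is used for that test. It may be unadjusted or adjusted for baseline variables, but not for app use or app content. Analyses with those variables are exploratory.
- The imputation at the end of Data Analysis applies to the 8-week value, which is T2 in arm A and T0 in arm B.
- Phase-2 pooled results are supportive, reported as estimates with 95% CIs, and do not establish hypothesis 1.

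This keeps change from baseline as the quantity analysed. It needs wording only, in the protocol or the analysis plan, and no new data. N stays 184, with 80.1% power at d = 0.5 and 64 completers per arm. The small cost is that the pooled change can no longer be used to claim the primary hypothesis.

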### Participant Classification

Data will be input into the R Minirand program (version 0.1.3; R Foundation for Statistical Computing) for randomization, and participants will be assigned to either the ThinkNinja for Epilepsy app arm (condition A) or the wait-list control arm (condition B) using minimization techniques. The prognostic factors over which the data will be minimized include age, sex at birth, and education level. Each prognostic factor will be minimized over two distinct categories: age (over 40 and under 40), sex at birth (male and female), and education level (below degree level and degree plus). Prognostic factors will have equal weighting in randomization. As there is not a requirement to blind this trial (ie, both clinicians and patients will be aware of whether they receive treatment or not), a deterministic approach is satisfactory; therefore, the significance level on which participants will be randomized is *P*>.99.

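### As written, no version of the primary QOLIE-10-P comparison adjusts for baseline variables alone, so precision available from data already collected is given up

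*Protocol article*

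**What the plan says.** The Outcomes and Variables section states: "The primary outcome is the QOLIE-10-P score". Data Analysis then gives the form of the comparison: "We will be comparing changes in quality of life (ie, QOLIE-10-P scores) from baseline to completion of the 8-week program". It is to be done "both unadjusted and adjusted for baseline characteristics, app use, and app content variables". Neither version is named as the primary one. The baseline characteristics are not listed, so the text does not say whether the baseline QOLIE-10-P score is among them.

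The cohort definitions in the same section fix the time points. Baseline is T0 in the app arm and T–1 in the wait-list arm. Week 8 is T2 in the app arm and T0 in the wait-list arm.

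On allocation, Participant Classification says: "The prognostic factors over which the data will be minimized include age, sex at birth, and education level", and "Each prognostic factor will be minimized over two distinct categories". Data Analysis does not name these three factors as covariates.

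Sample Size rests on a comparison of means: "It was performed using a 2-tailed *t* test of equal means at a significance level of .05". It assumes 80% power, a Cohen d of 0.5 and 30% dropout, giving 92 per arm and 184 in total. It does not say whether d is scaled to the SD of the score or to the SD of the change.

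**The concern.** Each of the two stated versions has a drawback.

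The unadjusted change makes no use of the regression of the week-8 score on baseline. It subtracts the whole baseline score whatever the correlation between the two measurements, and so carries baseline noise into the result when that correlation is modest.

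The adjusted version, read as one model, puts app use and app content beside the baseline variables. These are consequences of allocation. Under Study Procedure arm B receives the app only after 8 weeks, so during the comparison the app variables are absent by design in one arm and nearly collinear with arm. The SEM described later in Data Analysis treats them as mediators. A model that conditions on them does not estimate the total effect of being allocated to the app, and cannot be relied on to improve precision.

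The repeated-measures ANOVAs do not fill the gap. They are per-protocol sensitivity analyses, and no baseline covariate is described for them.

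What is at stake is precision in a trial sized for 80% power with no reserve beyond the dropout allowance.

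**Working it through.** **Inputs.** From Sample Size: two-sided α 0.05, power 80%, d=0.5, 1:1 allocation, 30% dropout, 184 in total. From Data Analysis: change from baseline to week 8. Assumed, because the article gives no value: ρ, the correlation between baseline and week-8 QOLIE-10-P, over 0.3 to 0.8, with equal SD σ at both times.

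**Step 1: reproduce the plan's figure.** A two-sample t test with d=0.5, two-sided α 0.05 and 80% power needs 63.77, so 64 per arm. 64/0.70 = 91.4, so 92 per arm, and 2 × 92 = 184. The planned number reproduces exactly. Power at 64 per arm is 80.1%.

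**Step 2: variances.**
- Change score: 2(1−ρ)σ²
- ANCOVA on baseline: (1−ρ²)σ² = (1−ρ)(1+ρ)σ²
- Ratio, ANCOVA to change: (1+ρ)/2, which never exceeds 1

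The proportional reduction is (1−ρ)/2: 35% at ρ 0.3, 25% at 0.5, 15% at 0.7, 10% at 0.8. Below ρ 0.5, 2(1−ρ) exceeds 1, so the change score is then less precise than a plain comparison of week-8 scores.

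**Step 3: power with 64 completers per arm, d=0.5 in SDs of the score.** The effective d is 0.5/√(2(1−ρ)) for change and 0.5/√(1−ρ²) for ANCOVA. At ρ 0.3 these are 0.5/√1.4 = 0.42 and 0.5/√0.91 = 0.52.

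| ρ | Variance ratio | Power, change | Power, ANCOVA | Completers per arm for 80%: change / ANCOVA |
|---|---|---|---|---|
| 0.3 | 0.65 | 66% | 84% | 89 / 59 |
| 0.4 | 0.70 | 73% | 87% | 77 / 54 |
| 0.5 | 0.75 | 80% | 90% | 64 / 49 |
| 0.6 | 0.80 | 88% | 94% | 52 / 42 |
| 0.7 | 0.85 | 95% | 98% | 39 / 34 |
| 0.8 | 0.90 | 99.3% | 99.7% | 27 / 24 |

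**Step 4: the same with d=0.5 in SDs of the change.** Change-score power is then 80% at every ρ. The effective d for ANCOVA is 0.5/√((1+ρ)/2), giving 94% (ρ 0.3), 92% (0.4), 90% (0.5), 88% (0.6), 86% (0.7) and 84% (0.8).

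**Step 5: cost in degrees of freedom.** With 128 completers a two-arm comparison has 126 residual degrees of freedom. Baseline score and three two-level factors take four, leaving 122. The power figures above ignore this small loss.

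**The case against.** The strongest reply is that the article is condensed. It does not say whether the listed covariates enter one model or successive ones, it leaves baseline characteristics undefined, and it names no estimator. Baseline QOLIE-10-P and the minimisation factors are natural members of that set. If the baseline score is a covariate, modelling change gives the same treatment estimate and standard error as modelling the week-8 score, so comparing changes does not rule ANCOVA out. This stands, and it limits the point to what is written. It does not remove the point, because the one adjusted version stated includes app use and app content. Even a generous reading of baseline characteristics yields a usable baseline-adjusted estimate only once those are taken out.

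It is also fair to say that this is efficiency, not error: the trial is described as exploratory, the unadjusted comparison is unbiased under randomisation, and the sample size is right.

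A reader might go further in two ways that the documents do not support.

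- **That the planned analysis is underpowered.** Power below 80% with 64 completers per arm requires both ρ under 0.5 and d scaled to the SD of the score. Sizing on QOLIE-10-P means and SDs leans towards the score, but does not settle it, and no ρ is given.
- **That leaving out the minimisation factors inflates the standard error by a known further amount.** Omitting factors on which allocation was balanced tends to make the standard error conservative. The size depends on what they explain of change, or of the week-8 score after baseline. Differencing or baseline adjustment already removes much of their effect, so that share may be near zero, and the documents give no figure for it.

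**Conclusion.** The point holds as one of specification and efficiency. As the text stands, no stated version of the primary comparison adjusts for baseline variables alone, and the version free of post-randomisation variables is never more precise than ANCOVA, apart from the few degrees of freedom spent. The direction is certain under equal variances. The size depends on ρ: the gain is substantial at 0.3 to 0.5 and small at 0.8 or above. Whichever SD d=0.5 refers to, ANCOVA has power above 80% with 64 completers per arm across the assumed range. The change score does so only for some combinations of ρ and scale. The planned 184 is not in error and the unadjusted change is not biased. The change is worth making because it costs almost nothing.

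**What to change.** In Data Analysis, designate one primary analysis: a linear model of week-8 QOLIE-10-P (arm A at T2, arm B at T0) on arm, baseline QOLIE-10-P (arm A at T0, arm B at T–1), age group, sex at birth and education level. Leave app use and app content out of it and move them to the exploratory analyses. Keep the unadjusted difference in change as supportive. Use the same form for GAD-7 and PHQ-9, each with its own baseline score.

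State in Sample Size whether d=0.5 refers to the SD of the score or of the change.

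The cost is wording and about four degrees of freedom. The baseline scores are already scheduled and the minimisation factors are needed for allocation, so no participants, visits or measures are added.

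### PGIC, a rating of change, is put into an ANOVA with a T0 level where it cannot be compared between arms, and that ANOVA gives neither PGIC nor MAQ an app-versus-waiting-list comparison

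*Protocol article*

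**What the plan says.** All statements are in the protocol article.

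- **Aims of This Study**, hypothesis 2, expects the intervention to improve "self-reported anxiety, depression, impression of change, and medication adherence, as measured by" the GAD-7, PHQ-9, PGIC and MAQ respectively.
- **Data Analysis**, on secondary outcomes: "The secondary outcome analysis will constitute analyzing the change in GAD-7 (ie, anxiety) and PHQ-9 (ie, depression) scores". The next sentence treats the other two differently: "we will be reporting on the results of the MAQ and PGIC, using descriptive statistics".
- **Data Analysis**, on descriptive results, promises a mean and SD of change from baseline for every outcome. PGIC is not excepted.
- **Data Analysis**, next step: "In addition to this, a sensitivity analysis that uses both the primary and secondary outcomes will be performed". For this, "a series of repeated-measures (2 × 4) analyses of variance (ANOVAs) will be performed in the first instance", with time levels given as "within-subject (ie, T0 vs T1 vs T2 vs T3) differences" and with "the secondary outcome measures (ie, GAD-7, PHQ-9, PGIC, and MAQ scores) as dependent variables" alongside the QOLIE-10-P. These tests are described as having 0.80 power at the .05 level, and the sensitivity analyses are to be per protocol.
- **Outcomes and Variables** defines T0 as baseline, with an additional T–1 for the waiting-list arm. T1 and T2 fall 4 and 8 weeks after the app is started, and T3 falls 8 weeks after the active period ends.

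**The concern.** A global impression of change has meaning only relative to some earlier point. The planned ANOVA needs a PGIC score at T0 in both arms and treats the two as the same starting level. In arm A, T0 comes at the start of the study, before the app. In arm B, T0 comes after an 8-week wait. A time effect or arm-by-time interaction built on that level would have no clear meaning. A change-from-baseline summary of PGIC has the same problem, since it would be a change in a rating of change.

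There is a second issue, which also covers MAQ. Hypothesis 2 is causal: it attributes improvement in impression of change and adherence to the intervention. The evidence for that is the randomised contrast between app and waiting list. For PGIC and MAQ the stated main analysis is descriptive, and the formal test that names them is one from which the waiting period has been left out. A significant time effect for either outcome could be read as support for hypothesis 2 when it is an uncontrolled before-and-after result.

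**Working it through.** No figure in the plan underlies this point, so the check sets the provisions side by side. The sample size does reproduce: 64 per arm for d = 0.5, two-sided .05 and 80% power; 64 / (1 − 0.30) = 91.4, so 92 per arm and 184 in total. Nothing below changes it.

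**Step 1: place the time points on a common clock.** Inputs are the definitions in Outcomes and Variables and the 8-week wait in Study Procedure. Weeks count from the first study assessment.

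| Time point | Arm A | Arm B |
|---|---|---|
| T–1 | none | week 0 |
| T0 | week 0 | week 8 |
| T1 | week 4 | 8 + 4 = week 12 |
| T2 | week 8 | 8 + 8 = week 16 |
| T3 | 8 + 8 = week 16 | 16 + 8 = week 24 |

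The Results section gives 16 weeks for arm B to complete the study, which does not reach week 24. The argument uses only T–1, T0 and T2 and does not depend on how that is resolved.

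**Step 2: what PGIC could mean at T0.** In arm A, T0 is the first assessment, so there is no earlier study point from which to rate change. In arm B, the only earlier study point is T–1, so a T0 rating could only describe the wait. The two T0 cells are not measurements of the same thing.

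**Step 3: does the unseen schedule matter?** The collection times by measure are in Figure 1, which is not available here. There are two cases:

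- PGIC is collected at T0. The arm A value has no study reference and is not comparable with arm B, so the 2 × 4 ANOVA is uninterpretable.
- PGIC is not collected at T0. One of the four time levels is missing, so the 2 × 4 ANOVA cannot be run. At most T1 to T3 (2 × 3) would remain.

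The specification fails in both.

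**Step 4: what the ANOVA compares.** Its levels are T0 to T3 in both arms, and T–1 is absent. From the table, arm B's T0 to T3 runs from the start of its app access onward.

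- The arm effect compares immediate with delayed access.
- The time effect is change after starting the app, pooled over arms, with no concurrent control.
- The interaction asks whether immediate and delayed starters follow different courses.

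None of these is app versus waiting list.

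**Step 5: where the randomised contrast lies.** At week 8, arm A is at T2 (treated) and arm B is at T0 (still untreated). Data Analysis already uses this mapping when it defines the per-protocol cohort: baseline is T0 in arm A and T–1 in arm B, and week 8 is T2 and T0. For MAQ, both the week-8 value and its baseline fit this mapping. For PGIC, the week-8 rating alone would serve, if it was taken in arm B and refers to the same period in both arms.

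**The case against.** The strongest reply is that there is no contradiction. The ANOVA paragraph opens as an addition to what precedes it and is labelled a sensitivity analysis, so a descriptive main report plus an extra exploratory test is a coherent plan. That stands. A reader might infer that the article forbids testing PGIC and MAQ and then tests them. The text does not say that description is the only treatment they receive. What remains is that, for these two outcomes, no formal main analysis is stated for a sensitivity analysis to check.

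Several other stronger readings also fail:

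- *The ANOVA is the only inferential test of these outcomes.* Subgroup analyses of change and a responder regression also draw on the secondary outcomes. None is a stated arm comparison of PGIC or MAQ, but they exist.
- *The randomised comparison is never made.* The first analysis phase compares arm A with the waiting list at 8 weeks, and descriptive statistics are promised for each outcome at each time point. Week-8 summaries by arm are therefore planned wherever the measure is collected. Only a formal comparison is unstated.
- *MAQ is unsuited to the ANOVA.* MAQ has a valid baseline. The missing control period affects every outcome in that ANOVA and is no reason to single MAQ out for removal.
- *PGIC has no pre-treatment meaning in either arm.* In arm B a T0 rating of the wait could be meaningful, and it is the comparator in the week-8 contrast.
- *PGIC is a single ordinal item and so unfit for a model of means.* The article does not describe its items, response scale or reference period.

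It is also fair to say that the trial is exploratory and that an article may leave details to an analysis plan. That does not rescue the PGIC ANOVA, because the article itself fixes the dependent variables and the time levels, and for PGIC the two do not fit together.

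**Conclusion.** The point holds in two parts. First, PGIC cannot be analysed as specified: the T0 level has no study reference in arm A and could only describe the wait in arm B, and the promised change from baseline has the same fault. This rests on PGIC being a rating of change, as its name in the article says, and holds whatever the schedule figure shows. Second, the T0 to T3 ANOVA provides no app-versus-waiting-list comparison for PGIC or MAQ, and the article names no formal randomised comparison for either, although hypothesis 2 claims an intervention effect on both.

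The reach is limited to two of the four secondary outcomes, with the T0 defect confined to PGIC. No effect on a numerical result can be calculated from the document. The main analyses of QOLIE-10-P, GAD-7 and PHQ-9 and the sample size are untouched by this point. It should be corrected because, followed as written, one planned analysis cannot be interpreted or cannot be run, and a within-arm time effect could be mistaken for evidence on hypothesis 2.

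**What to change.** 1. Take PGIC out of any analysis that has a T0 level or uses change from baseline, including the mean-and-SD summary of change.
2. State for MAQ and PGIC whether each is descriptive or formally compared.
3. If hypothesis 2 is to be assessed for them, compare the arms at week 8, arm A at T2 against arm B at T0. Adjust MAQ for its baseline (arm A T0, arm B T–1). Analyse PGIC by a method suited to its response scale and report an interval, provided that PGIC is collected in arm B at T0 and that both arms rate the same reference period.
4. If either condition fails, label PGIC descriptive only and draw no inferential conclusion from it. Hypothesis 2 need not be rewritten; the report should say that this component was not formally tested.
5. If MAQ stays in the T0 to T3 ANOVA, describe that result as change after starting the app, not as an effect against the waiting list.

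The cost is a change of wording and a small amount of extra analysis. No new data are needed if PGIC is already collected in arm B at T0. The added comparisons should be labelled as secondary results of an exploratory trial.
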